### Sample size

Sample size is determined primarily by the precision required for the primary model’s discrimination statistic [26, 27]. A minimum of 40 treatment failures is targeted for the five-predictor primary logistic regression model (muscle density, VAT area, age, sex, baseline MWD), yielding an events per variable (EPV) ratio of approximately 8. This EPV is recognized as modest, providing the primary rationale for the conservative four-predictor robustness check (Table 3, sensitivity analysis #7a). A supplementary power calculation confirms approximately 80% power to detect an odds ratio ≥2.0 per 10 HU decrease in skeletal muscle density (α ═ 0.05, two-tailed).

Assuming a treatment failure rate of 40%, reflecting the program non-completion component of the 40–50% failure rate reported in real-world European SET series [9] and a local institutional audit (approximately 38%); this 40% assumption captures both program non-completion and early revascularization combined, without separately modeling the functional non-response rate among completers. Accounting for 22% attrition from dropout and protocol non-completion, 128 patients must be enrolled to achieve 100 evaluable participants with 40 treatment failures. The IRONIC trial [8], which demonstrated that a significant proportion of claudicants managed conservatively required revascularization during follow-up, supports the clinical relevance of this failure rate, although it was not designed to quantify SET-specific non-response. A pre-specified sensitivity analysis reports model performance under a 30% failure rate scenario (approximately 30 failures, approximately 70% power). All precision-related conclusions are explicitly framed within the derivation cohort boundaries; external validation is necessary before any clinical translation.

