3	Alternative composite threshold: ≥100 m absolute MWD gain	Tests sensitivity to an absolute rather than relative distance criterion
4	Functional improvement component only (no revascularization criterion)	Isolates the predictive relationship with functional adaptation. Mandatory pre-specified secondary analysis; reported in all primary publications regardless of composite outcome result.
5	Revascularisation-free survival component only	Isolates the predictive relationship with intervention requirement. Mandatory pre-specified secondary analysis; reported in all primary publications regardless of composite outcome result.
6	Restriction to guideline-concordant revascularisation events only	Removes patient-preference-driven events to reduce confounding; specifically examines discordant cases (functional improvement achieved but revascularisation occurred)
7a	Four-predictor model: muscle density, VAT, age, sex (excluding baseline MWD)	Robustness check with an EPV approximately 10; tests stability of primary model estimates when baseline MWD is excluded
7b	Three-predictor model (muscle density, VAT, age; excluding sex)	Robustness check with an EPV approximately 13–14
8	Alternative muscle density threshold: 33 HU	Tests lower threshold sensitivity for myosteatosis classification (Martin et al. [21] value for BMI ≥ 25 kg/m^2^); see also Section 2.6
9	Alternative muscle density threshold: 41 HU [Martin et al. [21], BMI < 25 kg/m^2^ stratum]	Tests higher threshold sensitivity for myosteatosis classification; see Section 2.6
10	Alternative VAT threshold: --20 cm^2^ (110 cm^2^ M; 80 cm^2^ F)**†**	Tests sensitivity to a more conservative VAT threshold
11	Alternative VAT threshold: +20 cm^2^ (150 cm^2^ M; 120 cm^2^ F)**†**	Tests sensitivity to a more stringent VAT threshold
12	Adherent subgroup (≥30/36 sessions completed)	Per-protocol analysis to assess treatment-specific effects
13	30% treatment failure rate scenario (approximately 30 failures)	Reports model performance and power under a more optimistic clinical assumption
14	Expanded confounding model: primary five predictors plus ABI, smoking status, diabetes, Clinical Frailty Scale score, TASC II classification, SMI, SAT	Pre-specified secondary expanded model; EPV approximately 3–4 (acknowledged limitation); designated as robustness sensitivity analysis; tests whether primary predictor associations are independent of additional clinical confounders

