**Continuous predictor modeling**: In the primary model, skeletal muscle density and VAT area are utilized as continuous standardized z-scores. The nonlinearity of each continuous predictor is assessed using restricted cubic splines, with three to five knots selected based on the Akaike Information Criterion. Exploratory cutpoint derivation employing the Youden index (implemented via cutpointr) is conducted as a separate secondary exploratory analysis and is clearly labeled as hypothesis-generating; derived thresholds are not employed in the primary predictive model.

Internal validation is performed using bootstrap resampling (1000 samples), yielding optimism-corrected area under the curve (AUC), calibration slope, and calibration-in-the-large. The bootstrap resampling procedure encompasses the entire analytical pipeline, including nonlinearity assessment (spline knot selection); the same bootstrap samples are utilized for optimism correction across the full pipeline. For any exploratory cutpoint derivation, the derivation step is nested within a distinct independent bootstrap loop to prevent double-counting of optimism. A four-predictor model excluding baseline MWD (skeletal muscle density, VAT area, age, sex; EPV approximately 10) is included as a pre-specified robustness check (Table 3, sensitivity analysis #7a). A three-predictor model excluding sex (EPV approximately 13–14) is also part of the pre-specified robustness checks. For H3, the four-group sarcopenic obesity classification is incorporated as a categorical predictor in a similar model; H3 analyses are reported descriptively and interpreted as exploratory.

**Pre-specified secondary expanded model:** A secondary expanded confounding model is pre-specified, adjusting for the five primary predictors along with additional variables: ABI (continuous), smoking status (categorical), diabetes mellitus (binary), Clinical Frailty Scale score (ordinal), TASC II classification (categorical), SMI (continuous standardized z-score), and SAT area (continuous standardized z-score). This expanded model comprises approximately 12 predictors and, with 40 expected events, yields an EPV of approximately 3–4; this EPV limitation designates the expanded model as a robustness sensitivity analysis rather than a primary inferential tool (Table 3, sensitivity analysis #14). Results will be reported with 95% confidence intervals and interpreted cautiously due to limited EPV.

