Classification thresholds for the primary predictors (skeletal muscle density for H1; VAT area for H2) will be derived prospectively within this cohort and treated as pre-specified study outcomes rather than assumptions. For the binary primary composite outcome, optimal cut-points will be identified by maximizing the Youden index (J = sensitivity + specificity -- 1) using the cutpointr R package; 95% confidence intervals will be obtained via 1000-sample bootstrap resampling. Separate derivations will be conducted for skeletal muscle density (single threshold) and VAT area (sex-stratified: men and women analyzed independently to account for dimorphic adipose tissue distribution). For the secondary time-to-revascularization outcome, optimal cut-points will also be identified by maximizing the log-rank statistic via survminer::surv_cutpoint(), providing a time-to-event-appropriate complement to the Youden-index approach. Each threshold derivation will report the optimal cut-point value, Youden index, sensitivity, specificity, and 95% bootstrap CI. As thresholds will be derived from the same cohort used for evaluation, internal optimism is anticipated and explicitly acknowledged. Thus, all threshold-based classification results will be interpreted within the derivation-cohort framework, with external validation in an independent PAD multicenter cohort as the pre-specified mandatory next step prior to clinical translation. Literature-derived thresholds from non-PAD populations will be retained as pre-specified sensitivity analyses (Table 3) to facilitate transparent cross-referencing with existing oncological and metabolic literature.

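### The check offered for the modest events-per-variable ratio (#7a, with #7b) works by removing adjustment covariates, so it cannot separate overfitting from changed confounding control

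*Protocol article*

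**What the plan says.** The aim in the Introduction is independent prediction by muscle density (H1) and VAT area (H2). Under Primary model specification this becomes a fixed logistic model with density, VAT, age, sex and baseline MWD, and each hypothesis is tested there at p < 0.025.

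On size, the Sample size section states: "A minimum of 40 treatment failures is targeted for the five-predictor primary logistic regression model", "yielding an events per variable (EPV) ratio of approximately 8". It then says: "This EPV is recognized as modest, providing the primary rationale for the conservative four-predictor robustness check (Table 3, sensitivity analysis #7a".

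Table 3 defines the checks:

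- #7a: "Four-predictor model: muscle density, VAT, age, sex (excluding baseline MWD". Its rationale gives EPV of about 10 and adds that it "tests stability of primary model estimates when baseline MWD is excluded".
- #7b: "Three-predictor model (muscle density, VAT, age; excluding sex", with EPV of about 13–14.

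The Statistical analysis section repeats the second: "A three-predictor model excluding sex (EPV approximately 13–14) is also part of the pre-specified robustness checks".

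The same section derives VAT cut-points by sex, with "men and women analyzed independently to account for dimorphic adipose tissue distribution". The Introduction says that patients who walk less at baseline may gain proportionally more.

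**The concern.** Modest EPV raises a small-sample question: are the five coefficients inflated or unstable because there are few events per parameter? A useful check holds the estimand fixed and changes the way it is estimated. #7a and #7b do the reverse. They keep maximum likelihood and change what is adjusted for.

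If baseline MWD or sex is related both to the predictor and to failure, the OR for density or VAT shifts for a reason unrelated to overfitting. Agreement with the primary model then does not show that overfitting is absent, and disagreement does not show that it is present. The word conservative has no support in the text.

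This matters because the Discussion limits the conclusions to the sign and size of the predictor associations, so the ORs are the main product. The plan's own text gives reason to think that the dropped variables count: it treats VAT as sex-dependent, links baseline walking capacity to benefit, and defines functional success by a gain of 50 m or 50% of baseline MWD.

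**Working it through.** **1. The plan's EPV figures.** EPV = failures / predictors, with 40 failures from the Sample size section.

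- Primary model: 40/5 = 8.0 (stated: about 8).
- #7a: 40/4 = 10.0 (stated: about 10).
- #7b: 40/3 = 13.3 (stated: about 13–14).

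The figures reproduce, and the numerator never changes. Removing sex alone from the five predictors would leave four and EPV 10, so 13–14 is reached only if baseline MWD goes as well. The predictor list in Table 3 confirms this; the words excluding sex do not say it.

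**2. Simulation.** 100 evaluable patients, 40% failures, Wald tests at two-sided 0.025 (1.25% in each direction). Rejection rates come from 1,500 simulated cohorts per scenario and limiting ORs from 200,000 simulated subjects. Assumed, because the documents give none of it: 30% women; women 0.5 SD lower in density and 0.8 SD lower in VAT; density–MWD correlation 0.3 unless stated. ORs are for failure: density and MWD per SD decrease, VAT per SD increase, sex for women against men. The Monte Carlo standard error is about √(0.57 × 0.43/1500) = 1.3 percentage points near 57% and √(0.0125 × 0.9875/1500) = 0.3 points near 1.25%.

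| Assumed scenario | Result | Five predictors | #7a | #7b |
|---|---|---|---|---|
| No sex or MWD effect; H1, H2 null | Density OR | 0.99 | 0.99 | 0.99 |
| | Rejection, H1 direction | 1.1% | 1.0% | 1.2% |
| Women OR 2, low MWD OR 1.5; null | Density OR | 1.00 | 1.12 | 1.19 |
| | Rejection, H1 direction | 1.5% | 4.7% | 7.9% |
| | VAT OR | 1.00 | 1.00 | 0.90 |
| Women OR 2, low MWD OR 2, correlation 0.4; null | Density OR | 1.00 | 1.29 | 1.37 |
| | Rejection, H1 direction | 1.3% | 12.7% | 19.6% |
| Low MWD OR 0.67; null | Density OR | 1.01 | 0.89 | 0.89 |
| Low MWD OR 0.67; H1 true, OR 1.8 | Density OR | 1.81 | 1.57 | 1.57 |
| | H1 power | 56% | 37% | 38% |
| Women OR 2, low MWD OR 1.5; H2 true, OR 1.8 | VAT OR | 1.81 | 1.78 | 1.58 |
| | H2 power | 57% | 57% | 42% |
| Women OR 0.5, low MWD OR 0.67; null | VAT OR | 1.00 | 1.00 | 1.11 |
| | Rejection, H2 direction | 1.0% | 1.2% | 3.6% |

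Three things follow. Without confounding the models agree. With it, the density OR moves in #7a and #7b, up or down with the assumed signs. The VAT OR moves materially only in #7b, because #7a keeps sex.

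**3. Size of the problem being checked.** A second set of simulations assumed 70% men, men higher by 0.8 SD in VAT and 0.4 SD in density, low MWD OR 2 per SD, and density–MWD correlation 0.3. With a true density OR of 1.77, the mean estimates were:

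- five-predictor maximum likelihood: 1.87 (1.87/1.77 = 1.06);
- #7a: 2.16 (2.16/1.77 = 1.22);
- #7b: 2.23 (2.23/1.77 = 1.26).

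Five-predictor Firth estimates were 1.77–1.79. Here small-sample inflation is about 5–6%, and the reduced models sit 22–26% above the truth, including whatever small-sample inflation remains in them.

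**The case against.** The strongest reply is that these are labelled sensitivity analyses. Table 3 discloses that #7a leaves out baseline MWD, leaving out one covariate is an ordinary robustness check, and conservative may mean only fewer parameters. The Statistical analysis section also has a 1,000-sample bootstrap of the whole pipeline with all five predictors. Much of this stands, and it rules out four stronger readings that a reader might infer.

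- *That #7a and #7b put the H1 and H2 tests at risk.* They do not. The tests sit in the fixed five-predictor model, and Table 3 attaches no decision rule to either check. The rejection rates above show how far the supporting evidence could mislead, not the error rate of the study.
- *That the checks favour H1 and work against H2.* The documents give no density–MWD correlation and no effect of sex or MWD on failure. The one directional remark, in the Introduction, suggests that short walkers may do proportionally better; with that sign #7a and #7b weaken H1. Reversing the sex effect makes #7b support H2 falsely.
- *That both checks distort H2.* Only #7b does.
- *That these checks are the only protection against overfitting.* The bootstrap gives optimism-corrected AUC, calibration slope and calibration-in-the-large. No correction of the ORs is stated, however.

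It can also be said that penalisation belongs in the separate statistical analysis plan. Its absence from the article is not the point. The point is that the article names a method for a stated concern, and the method does not address that concern. The disclosure in Table 3 covers #7a; for #7b the omission of MWD must be worked out from the predictor list.

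**Conclusion.** The point holds in a limited form. #7a and #7b raise EPV from 8 to 10 and 13.3 solely by reducing adjustment. Where sex or baseline MWD confounds, they therefore estimate something other than the independent association in H1 and H2, and they cannot serve as evidence about overfitting. #7a and #7b can falsely support or falsely weaken H1; #7b can do either for H2.

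The size rests wholly on assumed correlations and covariate effects. It runs from nothing, without confounding, to a null density OR of 1.29 (#7a) or 1.37 (#7b) in the strongest scenario run. The primary inference is untouched. What is at stake is how the supporting analyses will be read, and that no stated coefficient-level check of small-sample bias keeps the full adjustment set. This is a cheap improvement, not a flaw in the primary analysis.

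**What to change.** 1. In Table 3, make the EPV robustness check the primary model itself (density, VAT, age, sex, baseline MWD) fitted by Firth penalised likelihood, and report its ORs beside the maximum-likelihood ORs.
2. In the Sample size section, delete the word conservative and refer to this model instead of #7a.
3. Keep #7a and #7b only as reduced-adjustment analyses. State in Table 3 and in the Statistical analysis section that #7b omits both sex and baseline MWD, and that neither is evidence on overfitting.

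Cost: a few lines of text and one extra fit in R; the primary model does not change. Firth Wald tests are slightly conservative. In the null scenarios above they rejected in the H1 direction in 0.5–1.2% of cohorts, against a nominal 1.25%. With H2 true at OR 1.8, power was about 52% against 57% for maximum likelihood, under the same assumptions. Because the Firth fit is a sensitivity analysis, this loss does not touch the primary tests.

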The primary aim of this study is to determine whether L3 CT-derived skeletal muscle density and VAT area independently predict composite SET treatment success at three months in patients with Fontaine IIa–IIb intermittent claudication. Two co-primary hypotheses are tested: H1 proposes that lower skeletal muscle density per 1 standard deviation (SD) decrease will predict treatment failure; H2 posits that higher VAT area per 1 SD increase will predict treatment failure. H3, which states that the sarcopenic obesity phenotype is associated with the lowest treatment success rates across body composition phenotype groups, is designated as a secondary/descriptive hypothesis and is not included in the family-wise Bonferroni correction for the co-primary analyses. This is a prospective observational derivation cohort study, hereafter referred to as CT Body Composition as Predictor of Exercise Therapy Outcome in PAD (COMPOSE-PAD); external multicenter validation is the pre-specified and required next step before clinical translation.

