### Statistical analysis

**Analytical hierarchy:** In all primary analyses (H1 and H2), skeletal muscle density and VAT area are treated as continuous standardized z-scores (mean = 0, SD = 1). This approach serves as the foundation for all inferential conclusions. All classification thresholds—whether derived from cohorts via Youden index maximization (cutpointr) or from literature pertaining to non-PAD populations (Martin et al. [21]; general population VAT reference values [23, 24])—are established post-hoc and are explicitly designated as exploratory and hypothesis-generating. These thresholds do not influence the primary predictive model and necessitate external validation in an independent PAD cohort prior to any clinical application. This distinction is consistently maintained throughout the statistical analysis section.

All analyses are conducted using International Business Machines (IBM) Statistical Package for the Social Sciences (SPSS) Statistics, version 30 (IBM Corp., Armonk, NY) and R version 4.3 (R Foundation for Statistical Computing, Vienna, Austria; packages: rms, cmprsk, mice, boot, cutpointr, survminer). The complete statistical analysis plan is pre-registered at ClinicalTrials.gov before database lock, and no post-hoc modifications to the primary analysis are allowed.

**Primary model specification:** The primary model for H1 and H2 is a pre-specified multivariable logistic regression with binary treatment success (success/failure) as the outcome, incorporating five predictors: skeletal muscle density (continuous standardized z-score), VAT area (continuous standardized z-score), age (continuous), sex (binary), and baseline MWD (continuous). SMI and SAT are excluded from the primary model; they are included only as covariates in the pre-specified secondary expanded model. This model specification is fixed and will not be altered once data collection begins.

The two co-primary hypotheses (H1, H2) are tested at a Bonferroni-corrected significance threshold of p < 0.025 per hypothesis (family-wise α ═ 0.05). Hypothesis 3 (H3), pertaining to sarcopenic obesity, is classified as a secondary/descriptive hypothesis and is not subject to family-wise correction. Secondary Spearman correlation analyses between continuous body composition parameters and secondary functional outcomes will be reported with Benjamini-Hochberg false discovery rate correction (q < 0.05).

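### The stated 80% power for H1 is computed at two-sided alpha 0.05, but H1 is tested at 0.025, where the same inputs give about 71%

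*Protocol article*

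**What the plan says.** The Sample size section of the protocol article bases the sample size primarily on the precision of the discrimination statistic and targets 40 treatment failures. It plans for 100 evaluable participants out of 128 enrolled, at a failure rate of 40%. It then adds a power statement for H1: "A supplementary power calculation confirms approximately 80% power to detect an odds ratio ≥2.0 per 10 HU decrease in skeletal muscle density", with alpha given as 0.05, two-sided. For a 30% failure rate (about 30 failures) it gives about 70%.

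The Statistical analysis section, under the primary model specification, says that the two co-primary hypotheses "are tested at a Bonferroni-corrected significance threshold of p < 0.025 per hypothesis (family-wise α ═ 0.05"). The test of H1 is the muscle density term in a logistic model that also contains VAT area, age, sex and baseline MWD.

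The article gives no power at 0.025, no SD for muscle density, and no statement on whether the 80% allows for correlation between muscle density and the other four predictors.

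**The concern.** The power statement and the decision rule use different significance levels. The article prints both numbers, so this is not a detail left to a fuller document. It contains no other power calculation, and nothing elsewhere in it reconciles the two levels.

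The consequence is in how a null result would be read. If H1 misses p < 0.025, a reader relying on the Sample size section would take the study to have had a 20% chance of missing an odds ratio of 2.0 per 10 HU. On the plan's own inputs that chance is nearer 29%.

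**Working it through.** **Inputs from the article.** Power about 80% at two-sided 0.05, odds ratio 2.0 per 10 HU, 100 evaluable, 40 failures, 128 enrolled, and about 70% power with 30 failures (all Sample size); test level 0.025 per hypothesis (Statistical analysis).

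**Step 1. Can the plan's 80% be reproduced?** For a continuous predictor in logistic regression,

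power = Φ( √(N·p·(1−p)·(1−R²)) × ln(OR per SD) − z(1−α/2) ),

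where R² is from the regression of muscle density on the other predictors. The article gives neither the SD nor R², so the 80% can only be solved backwards. With N = 100, p = 0.40 and R² = 0, √(100 × 0.40 × 0.60) = 4.899. Power of 80% at 0.05 needs ln(OR per SD) = (1.960 + 0.842)/4.899 = 0.572, that is OR 1.77 per SD. Since ln 2 = 0.693 per 10 HU, the implied SD is 0.572/0.0693 = 8.25 HU.

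This value depends on the formula. In simulated univariable logistic regressions with 100 participants and 40% failures, an SD of 8.75 HU gave:

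| Test | Power at 0.05 | Power at 0.025 |
|---|---|---|
| Wald | 79% | 68% |
| Likelihood ratio | 81% | 71% |

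**Step 2. Change only the significance level.** The SD is not needed here. Power of 80% at two-sided 0.05 implies a noncentrality of 1.960 + 0.842 = 2.802. The critical value at two-sided 0.025 is 2.241, so

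power = Φ(2.802 − 2.241) = Φ(0.560) = 71.2%.

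Reading the stated figure as 78% gives 68.8%; reading it as 82% gives 73.7%.

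**Step 3. The 30% failure scenario.**
- From the stated 70%: noncentrality 1.960 + 0.524 = 2.484, and Φ(2.484 − 2.241) = Φ(0.243) = about 60%.
- From the 80%, with N held at 100: 2.802 × √(0.21/0.24) = 2.621, which gives 75% at 0.05 and 65% at 0.025.
- From the 80%, scaled by events (30/40): 2.802 × √0.75 = 2.426, which gives 68% at 0.05 and 57% at 0.025.

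The stated 70% lies between 68% and 75%, so it has no separate error. It has only the same mismatch of significance level.

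**Step 4. What could move the 71%.**

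| Assumption (not stated in the article) | Power for H1 at 0.025 |
|---|---|
| 80% already allows for covariates, N = 100 | 71% |
| 80% was unadjusted, R² = 0.1, N = 100 | Φ(2.802·√0.9 − 2.241) = 66% |
| 80% was unadjusted, R² = 0.2, N = 100 | Φ(2.802·√0.8 − 2.241) = 60% |
| 80% was unadjusted, R² = 0.3, N = 100 | Φ(2.802·√0.7 − 2.241) = 54% |
| All 128 analysed, 40% failures, no covariate loss | Φ(2.802·√1.28 − 2.241) = 82% |
| All 128 analysed, 80% was unadjusted, R² = 0.3 | 66% |

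An SD above about 9 HU would also bring power at 0.025 to 80% or more with N = 100 and R² = 0: 9 HU gives 79% and 10 HU gives 88%. The printed figure at 0.05 would then itself be wrong, because the same SDs give 86% and 92% there.

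**The case against.** The best defence is that the calculation is labelled supplementary and does not set the sample size. The Discussion also concedes limited precision for discrimination and confines conclusions to the direction and magnitude of associations. This stands as a limit on the damage: no analysis or enrolment number depends on the 80%. It does not remove the inconsistency. H1 and H2 still carry a formal significance rule, and the concession on precision does not address the significance level.

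A second defence is that more than 100 patients may be analysed. Non-adherent patients are retained, non-completion counts as failure, withdrawal-visit data are used and the composite outcome is imputed. This also stands, and it is why 71% is not a ceiling. The Sample size section nevertheless plans on 100 evaluable participants, and 71% is the figure on that basis.

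Three stronger readings are tempting and not supported:

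- **That true power is 54% to 71%.** The lower values need assumed R² values and a calculation that ignored covariates. The article does not say which was done. Only SD × √(1−R²) can be recovered from the 80%; an SD of about 9.2 HU with R² = 0.2 gives the same figure, already adjusted.
- **That power per 10 HU is wrong because H1 is worded per 1 SD.** Rescaling a continuous predictor leaves its test, p-value and power unchanged. The missing SD prevents a check of the 80%, but the choice of unit is not an error.
- **That Bonferroni is a mistake.** It validly controls the family-wise error. A less conservative procedure is a preference.

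**Conclusion.** The power statement is wrong as written. It is given at 0.05, while H1 is tested at 0.025, and at that level the plan's own 80% corresponds to about 71% (69% to 74% allowing for rounding). The figure for the 30% failure scenario falls from about 70% to about 60%, with a range of 57% to 65% depending on how that scenario is scaled from the 80%.

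The 71% assumes that the stated 80% is correct for 100 evaluable participants with 40 failures. It applies to H1 only; the article gives no power for H2, and none should be inferred from this figure. The actual power could be lower or higher for the reasons tabulated above, and the article does not settle which. The error affects what the study claims about itself, not the validity of its tests.

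**What to change.** In the Sample size section, restate the supplementary power for H1 at two-sided 0.025 for both the 40% and the 30% failure scenarios. Give the assumed SD of muscle density in HU, the number of participants analysed, and whether correlation with VAT area, age, sex and baseline MWD is allowed for. If the inputs behind the present 80% stay as they are, the text should read about 71% and about 60%.

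The cost is wording and a less favourable figure. It can be done before enrolment, planned for June 2026. If the sponsor would rather keep 80% at 0.025 on the same inputs, the number of evaluable participants rises by the factor ((2.241 + 0.842)/2.802)² = 1.21, to about 122. That is 122/0.78 = about 157 enrolled at 22% attrition, with no further covariate loss.

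Optionally, test H1 and H2 with Holm's step-down: the smaller p-value against 0.025 and, if that is significant, the other against 0.05. This keeps the family-wise error at 0.05 and is never less powerful than Bonferroni. If both effects were equally strong and the tests independent, which is an assumption, power per hypothesis would be 0.71 + (0.80 − 0.71) × 0.71 = about 77%. The small downside is that simultaneous confidence intervals become less simple.

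### The stated power of about 80% for muscle density uses alpha 0.05, but H1 is tested at 0.025; on the protocol's own figure the planned test has about 71%

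*Protocol article*

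**What the plan says.** The Sample size section of the protocol article bases the study size mainly on precision of the model's discrimination and on a target of 40 failures for five predictors. It then adds a power calculation, which it calls supplementary, and reports "approximately 80% power to detect an odds ratio ≥2.0 per 10 HU decrease in skeletal muscle density" with "α ═ 0.05, two-tailed". The numbers behind it are that "128 patients must be enrolled to achieve 100 evaluable participants with 40 treatment failures". The same section gives a second power, about 70%, for a scenario with about 30 failures, and does not restate an alpha for it.

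The Statistical analysis section says the two co-primary hypotheses are "tested at a Bonferroni-corrected significance threshold of p < 0.025 per hypothesis", with a family-wise alpha of 0.05. The test is made in a logistic model with muscle density, VAT area, age, sex and baseline MWD. The Introduction puts H1 on the SD scale: "H1 proposes that lower skeletal muscle density per 1 standard deviation (SD) decrease will predict treatment failure". The Discussion lists the Bonferroni correction among the strengths of the protocol.

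**The concern.** Muscle density is the H1 predictor, so the power sentence is about H1. It is computed at twice the significance level at which H1 will be judged. The protocol takes credit for the multiplicity correction, but the stated power does not bear its cost.

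The risk lies in how a null result would be read. If H1 is not significant at 0.025, a reader of the Sample size section would set that against a 20% chance of missing the assumed effect. On the protocol's own figure the chance is about 29%. CT muscle density could then be discounted more firmly than the data justify.

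**Working it through.** **Inputs from the protocol article.** Power about 80% at two-sided alpha 0.05; OR 2.0 per 10 HU; 100 evaluable patients; 40 failures (Sample size). Alpha 0.025 per hypothesis; five-predictor logistic model (Statistical analysis). The SD of muscle density and its correlation with the other predictors are not given.

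**1. Can the 80% be reproduced?** Use the usual normal approximation for a continuous predictor in logistic regression:

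power = Φ( |ln OR per SD| × √(n·p·(1−p)·(1−R²)) − z(1−α/2) ), with ln OR per SD = ln 2 × SD/10.

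With n = 100 and p = 0.40, n·p·(1−p) = 24. The result depends on the missing SD. At alpha 0.05 with R² = 0, power is:

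| SD (HU) | 6 | 7 | 8 | 9 | 10 |
|---|---|---|---|---|---|
| Power | 53% | 66% | 77.5% | 86% | 92% |

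Exactly 80% needs an SD of 8.25 HU (OR 1.77 per SD) if R² = 0. It needs an SD of 8.7 to 9.9 HU if R² is 0.1 to 0.3. The 80% is therefore attainable but cannot be confirmed from the article, and it does not reveal whether covariates were allowed for. The steps below take it as given.

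**2. Change only the alpha.** A test with 80% power at two-sided 0.05 has noncentrality 1.960 + 0.842 = 2.802. At two-sided 0.025 the critical value is 2.241, so

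power = Φ(2.802 − 2.241) = Φ(0.560) = 71.2%.

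This step needs neither an SD nor an R². If the stated figure means 78% or 82%, the result is 68.8% or 73.7%.

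**3. The 30-failure scenario.** If its 70% was also computed at 0.05, the noncentrality is 1.960 + 0.524 = 2.484, and power at 0.025 is Φ(2.484 − 2.241) = Φ(0.243), about 60%. This again takes the protocol's figure as given. The effect that yields 80% with 40 failures would, by the formula in step 1, yield 74.6% with 30 failures at 0.05.

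**4. Conditional step: covariate correlation.** Suppose the 80% assumed no correlation of muscle density with VAT, age, sex and baseline MWD. Then the noncentrality shrinks by √(1−R²). With R² assumed, since the article gives none:

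| Assumed R² | Noncentrality | Power at 0.025 |
|---|---|---|
| 0 | 2.802 | 71% |
| 0.1 | 2.658 | 66% |
| 0.2 | 2.506 | 60% |
| 0.3 | 2.344 | 54% |

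As a cross-check, Wald tests were simulated in a five-predictor logistic model (4,000 replicates per R², SD 8.25 HU, alpha 0.025). Power was 63%, 58%, 53% and 46% for R² of 0, 0.1, 0.2 and 0.3. The approximation does not exaggerate the loss.

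**The case against.** The strongest reply is that the sample size does not rest on this figure. The article calls the power calculation supplementary, sizes the study on precision, confines its conclusions in the Discussion to direction and magnitude of associations, and requires external validation before clinical use. That stands, and it lowers the severity. It does not make the sentence right: a supplementary power figure should still describe the test that will be run. Both alphas are fixed in this article, so a separate analysis plan would not remove the mismatch.

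A second reply is that the analysis set may exceed 100. Non-adherers are retained, non-completion counts as failure, and missing outcomes are imputed. With 128 patients, 40% failures and the SD of 8.25 HU, the formula gives about 82% at 0.025 for R² = 0, and 78%, 72% and 66% for R² of 0.1, 0.2 and 0.3. This is an upper bound, because imputed outcomes add little information. The protocol also ties its own target to 100 evaluable patients and 40 failures.

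Three stronger readings are tempting, and the article does not support them:

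- **That the 80% was computed for an unadjusted predictor, so true power is 54-66%.** The section does not describe covariate handling. The SD of 8.25 HU comes from setting R² to zero, so it cannot serve as evidence that no adjustment was made. If the 80% already allowed for covariates, 71% is the end figure, and a further deduction would count them twice.
- **That an effect per 10 HU contradicts a hypothesis per SD.** This is a linear rescaling and leaves the test and its power unchanged.
- **That the absent SD, R² and H2 power are errors.** An article may leave such detail to the full protocol or analysis plan.

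**Conclusion.** The power sentence is wrong as written, because it quotes power at alpha 0.05 for a hypothesis tested at 0.025. On the protocol's own 80%, the planned test of H1 has about 71% power (69-74% allowing for rounding), and the 30-failure scenario about 60% if it used the same alpha. These figures rest only on the stated powers and the two alphas. The lower values of 66%, 60% and 54% hold only if the 80% ignored covariate correlation and R² is 0.1, 0.2 or 0.3. They are a sensitivity range on assumed inputs and should not be reported as the power of the design. Severity is moderate.

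**What to change.** Recompute both power figures in the Sample size section at two-sided alpha 0.025 for the five-predictor model. Use the authors' own SD of muscle density and their own assumption about its correlation with the other four predictors, and state both. Until that is done, about 71% is the figure the present text implies for the 40-failure case.

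Preferably, add the minimum detectable odds ratio per SD at the same alpha, which would also cover H2. As a guide, exp( (2.241 + 0.842) / √(24·(1−R²)) ) gives 1.88 for R² = 0, 2.02 for 0.2 and 2.12 for 0.3, for 80% power with 100 patients and 40 failures.

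The cost is a sentence or two and a less favourable stated power. No change in enrolment is needed, and none should be inferred. The change is easily made now, since enrolment has not begun.
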